**Methods/Design:**

Patients with PTSD will be recruited via the research arm of a not-for-profit clinical and research unit in Australia and randomised to a treatment group or waitlist control group. The minimum sample size for each group (alpha 0.05, power 0.80 for a *g* of 0.47) was identified as 72, but 10 % more will be recruited to hedge against expected attrition. PTSD diagnosis will be determined using the PTSD module from the Mini International Neuropsychiatric Interview version 5.0.0. The PTSD Checklist – Civilian version (PCL-C) will be used to measure PTSD symptoms (the primary outcome measure), with the Intolerance of Uncertainty Scale 12-item version (IUS-12) and the Emotion Regulation Questionnaire (ERQ) used to measure intolerance of uncertainty and emotion regulation, respectively. The PCL-C will be administered to the treatment group before each lesson of the PTSD program and at 3-month follow-up. The IUS-12 and ERQ will be administered before lessons 1 and 4, at post-treatment and at 3-month follow-up. The waitlist control group will complete these measures at week 1, week 5 and week 11 of the waitlist period. PTSD program efficacy will be determined using intent-to-treat mixed models. Maintenance of gains will be assessed at 3-month follow-up. Mediation analyses using PROCESS will be used to examine the association between change in PTSD symptoms over treatment and change in each of IU and emotion regulation ability in separate analyses.

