### Statistical methods

Power calculations were informed by calculation of effect size data from Spence et al. [20], providing a between-group effect corresponding to Hedges’ g of 0.47. The minimum sample size for each group (alpha set at 0.05, power at 0.80) was identified as 72, but at least 10 % more will be recruited to hedge against expected attrition. All analyses will be conducted at conclusion of the trial period (i.e. after all participants in the treatment group have completed the iCBT program). Significance testing of group differences regarding demographic data and pre-treatment measurements will be conducted using analysis of variance (ANOVA) and χ2 where the variables consist of nominal (or categorical) data. Intent-to-treat (ITT) mixed models using restricted maximum likelihood (REML) estimation will be used to account for missing data due to participant drop-out. Mixed models do not assume that the last measurement is stable (the last observation carried forward assumption) [63]. REML models are appropriate for RCTs with multiple time points and pre-to post-only designs [64]. The assumption that data are missing at random (MAR) will be evaluated using binary logistic regression to predict drop-out (0 = no drop-out, 1 = drop-out) and by comparing these two groups on baseline measures. Significant effects will be followed up with pairwise contrasts comparing mean pre-treatment to mean post-treatment scores. Complete-case analyses of the primary hypotheses using data from participants who complete all six lessons of the PTSD program will also be conducted. The effect of potential treatment moderators (e.g. time post-trauma, number of traumatic events) will be evaluated by including baseline variables of interest as a covariate and interaction term in separate mixed models analyses. Analyses will be performed in IBM SPSS version 21. Effect sizes will be calculated between groups (Hedges’ g) and within groups (Cohen’s d, adjusting for the repeated measures correlation) using the pooled standard deviation and adjusted for sample size.

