Mediation analyses will be used to examine the association between change in PTSD symptoms over treatment and change in each of IU and emotion regulation in separate analyses. Tests of the indirect effects (mediation) will be conducted using PROCESS [65]. This method was chosen over the causal steps approach [66] based on recent research advocating the use of modern statistical approaches to quantify intervening variable models [67]. As recommended, particularly for small samples, estimates of indirect effects will be generated using bootstrapping analysis see [68, 69]. Bootstrapping is a nonparametric resampling method that generates an estimate of the indirect effect, and does not require assumptions about the shape of the sampling distribution that underlie the Sobel test. In bootstrapping analysis, the most stringent test of an indirect effect (mediation) is if the 95 % bias corrected and accelerated confidence intervals for the indirect effect do not include the value of 0. When zero is outside of the 95 % confidence interval estimate, the indirect effect is declared statistically different from zero at *p* < 0.05 (two-tailed), indicating that the effect of the independent variable on the dependent variable is contingent upon the effect of the proposed mediator [68]. In the current study, PROCESS for SPSS will be used to estimate 5000 bias-corrected bootstrap 95 % confidence intervals.

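### The mediation analysis is assigned to PROCESS with no missing-data step, so it would use complete cases only, while the efficacy analysis is built to handle drop-out

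*Protocol article*

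**What the plan says.** For efficacy, the abstract's Methods/Design paragraph states "PTSD program efficacy will be determined using intent-to-treat mixed models". Statistical methods gives the reason: "mixed models using restricted maximum likelihood (REML) estimation will be used to account for missing data due to participant drop-out". It adds a check on the missing-data mechanism: "The assumption that data are missing at random (MAR) will be evaluated using binary logistic regression to predict drop-out".

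For mediation, the same section names a different tool. The analyses examine "the association between change in PTSD symptoms over treatment and change in each of IU and emotion regulation in separate analyses", and "Tests of the indirect effects (mediation) will be conducted using PROCESS". The interval is fixed too: "PROCESS for SPSS will be used to estimate 5000 bias-corrected bootstrap" 95% confidence intervals. No imputation, likelihood-based or other missing-data step is attached to these analyses.

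The mediators are measured mid-course as well as before and after treatment: "The IUS-12 and ERQ will be administered before lessons 1 and 4, at post-treatment and at 3-month follow-up". Table 1 shows mid-treatment PCL-C, IUS-12 and ERQ in both arms (waitlist at week 5). The only analysis labelled complete-case is a supplementary one of the primary hypotheses, in participants who finish all six lessons.

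**The concern.** The plan treats drop-out as a problem that needs a model for efficacy, and then tests mediation with a tool that has no such provision. Change over treatment needs a post-treatment value of both mediator and outcome. A participant who stops halfway contributes to the efficacy model through the scores already given, but contributes nothing to a regression of change on change.

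Two things are at stake. One is precision, because partial records are discarded. The other is validity. If leaving depends on how the PCL-C moved early in treatment, the data can be missing at random for a mixed model that contains those scores, but not for a pre-to-post regression that omits them. The efficacy and mediation results would also describe different sets of participants, and the mediation result would be complete-case without being labelled so.

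**Working it through.** **1. Which participants each analysis uses.** The efficacy model uses anyone with a PCL-C score. The mediation regressions use only participants with post-treatment PCL-C and the relevant post-treatment mediator. This rests on two things outside the text: PROCESS deletes incomplete cases, which is a property of the named software, and change is read as post-treatment minus pre-treatment.

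**2. Numbers left.** The plan's own figure first. For an effect "corresponding to Hedges’ g of 0.47", with two-sided alpha 0.05 (sidedness assumed) and power 0.80, n = 2 × 2.8016² / 0.47² = 15.70 / 0.2209 = 71.1, rounded up to 72 per group. This reproduces the stated 72. Adding 10% gives 79.2, so 80 per group.

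With assumed losses, complete records per group out of 80 are:

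| Loss | Complete per group | Power for a simple group difference, g = 0.47 (scale only) |
|---|---|---|
| 10% | 72 | 0.81 |
| 20% | 64 | 0.76 |
| 30% | 56 | 0.70 |
| 40% | 48 | 0.63 |

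**3. Bias, first model (all values assumed).** X is the arm, ΔM the mediator change and ΔY the PCL-C change, in SD units:

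- ΔM = −0.5X + e, with SD 1
- ΔY = −0.2X + 0.5ΔM + e, with SD 0.87
- early PCL-C change = 0.7ΔY + noise, with SD 0.7

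The true indirect effect is −0.5 × 0.5 = −0.25 (−0.249 in the simulated full data of 1,000,000) and the direct effect is −0.20. Drop-out depends on early change with an odds ratio of 1.65 to 2.7 per SD. In the first two rows it does so in the treatment arm only, with 5% random loss on the waitlist.

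| Who leaves | Indirect effect, 10% loss | Indirect effect, 30% loss |
|---|---|---|
| Poor early responders, treatment arm | −0.256 to −0.262 | −0.273 to −0.287 |
| Good early responders, treatment arm | −0.239 to −0.229 | −0.221 to −0.199 |
| Poor early responders, both arms alike | −0.246 to −0.242 | −0.244 to −0.235 |

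Relative to −0.249:

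- First row: 0.256/0.249 to 0.262/0.249 is 3–5% too large at 10% loss. At 30% it is 10–15% too large. At 20% the range is −0.265 to −0.275, or 6–10%.
- Second row: 4–8% too small at 10% and 11–20% too small at 30%.
- Third row: 1–3% too small at 10% and 2–6% at 30%.

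The direct effect is more exposed. In the first scenario it is overstated by about 14–27% at 10% loss and roughly 40–75% at 30%. With both arms alike it stays at −0.20 to −0.21.

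**4. Bias against sampling error.** In the same model with 72 per arm, SE(ab) ≈ √(b²·SE_a² + a²·SE_b²), where SE_a² = 2/72 = 0.0278 and SE_b² = 0.87²/141 = 0.0054. So SE ≈ √(0.25 × 0.0278 + 0.25 × 0.0054) = 0.091. At 10% loss the shift in the first scenario is 0.007 to 0.013, which is 0.08 to 0.14 SE. At 30% it is 0.024 to 0.038, about 0.3 to 0.4 of that SE.

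**5. Second model (assumed).** Here post-treatment scores are adjusted for baseline, with a = −0.5, b = 0.4 and direct effect −0.27. Random drop-out, and drop-out depending only on baseline PCL-C (which is in the model), gave essentially no bias. Drop-out depending on mid-treatment PCL-C moved the indirect effect by about −1% to +6%. The direct effect moved to as far as −0.35, at 40% treatment-arm and 15% waitlist loss.

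**The case against.** The strongest reply is that this is a silence in a condensed article. Naming PROCESS does not rule out imputing first, and an analysis plan that is not shown may say so. That is possible. But the article does fix the tool, the bootstrap type, the number of resamples and the decision rule. Followed as written, those give a complete-data analysis.

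It can also be said that the article does not define how change is computed, so mid-treatment scores are not formally excluded. That stands, and is why post-minus-pre is listed above as an assumption.

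A reader might infer that the plan abandons intent-to-treat for mediation. The document does not support that: it ties the intent-to-treat models to efficacy and never promises them for mediation. This is an inconsistency of approach, not a contradiction in the text.

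A reader might also infer that the mediation results will be biased towards treatment. That does not follow either. It requires poor early responders to leave the treatment arm selectively, and nothing in the article favours that over the opposite pattern, which reverses the sign.

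Finally, the declared test is of the indirect effect, where the bias at about 10% loss would rarely change whether the interval excludes zero. Hypotheses 3 and 5 are secondary, and the Discussion presents these findings only as pointers to later research. All of this limits the weight of the point without removing it.

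**Conclusion.** The point holds as a modest, inexpensive improvement to a secondary analysis. As written, mediation would rest on participants with complete post-treatment data, while efficacy rests on a model chosen to accommodate drop-out. Loss of precision is the surer cost. Bias in either direction is possible if drop-out depends on mid-treatment scores. For the indirect effect it is small at about 10% loss (3–5%, about 0.1 SE, in the first scenario) and grows with attrition; the direct effect can move more. It is small or absent if drop-out is random, depends only on baseline values in the model, or acts alike in both arms.

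These sizes rest on assumed paths, drop-out mechanisms and attrition rates, because the article gives no rate beyond its recruitment margin. The primary endpoint and the sample size are not affected.

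**What to change.** Make the main mediation analysis include all randomised participants. Either multiply impute post-treatment PCL-C, IUS-12 and ERQ separately by arm, from baseline and mid-treatment values of the same three measures, or fit the path model by full-information maximum likelihood with the mid-treatment scores included. Bootstrap the indirect effect within whichever is chosen. Report the complete-data PROCESS result as a sensitivity analysis, labelled as such.

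No new data are needed; the cost is a few hours of analysis work. The downside is somewhat more computing, and software beyond PROCESS to pool imputations or fit the path model.

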### Ethics and dissemination

Staff associated with the project are aware of, and will adhere to, the National Statement on Ethical Conduct in Human Research (National Health and Medical Research Council, 2007). The current trial protocol has been approved by the Human Research Ethics Committee of St Vincent’s Hospital, Sydney, Australia. The trial is registered as ACTRN12614001213639.

All members of the research team who provide intellectual input to the trial design, execution, or write-up will be acknowledged as an author on any publications.

## Discussion

The current RCT will test the efficacy of an iCBT intervention for PTSD. It seeks to replicate previous efficacy findings [20, 23] of iCBT for PTSD in a formally assessed PTSD sample from the general population. Moreover, it will examine the relationship between PTSD symptom change following treatment and changes in IU and emotion regulation. As such, results from the proposed RCT may point to future lines of enquiry into the role of these constructs in the mechanism of PTSD symptom change during CBT.

Notwithstanding the potential utility of the proposed RCT, the following potential limitations are noted. The control group in the current study is a waitlist control, rather than an active treatment control. Therefore, it will not be possible to eliminate a potential placebo effect. Moreover, the results will not speak to the relative utility of iCBT for PTSD compared to an alternative treatment approach or modality. These will be questions for future research. Further, while the trial will examine potential change in IU and emotion regulation ability, the iCBT program was not written to specifically target either of these constructs. As such, results will not permit definitive conclusions as to how treatment components impact these constructs. The current RCT will use DSM-IV PTSD diagnostic criteria and associated standardised assessment instruments, as validated DSM-5 measures were not available when recruitment began for the current project. While items reflecting the three additional DSM-5 PTSD symptoms from the PCL-5 have been included, it is important to note that formal diagnostic and associated self-report measures do not measure DSM-5 PTSD criteria specifically. We note that while having different clinicians conduct pre-treatment and follow-up interviews controls for bias, it may introduce inter-rater variability.

Finally, history of child sexual and/or physical abuse is not an exclusion criterion in the current study. This approach was undertaken to maximise the generalisability of the study findings, given the prevalence of early life abuse histories in those suffering from PTSD e.g. [5]. It is noted that emerging evidence suggests emotion regulation skills training may be required prior to trauma-focused treatment for survivors of child trauma in order to optimise their potential benefit from trauma-focused treatment e.g. [31]. Accordingly, some national treatment guidelines suggest a period of emotion regulation or stabilisation prior to trauma-focused CBT for survivors of child abuse or other repeated/prolonged exposure to trauma [10, 11]. However, there is evidence that trauma-focused treatment may have utility for such people even in the absence of emotion regulation training [38, 70, 71]. Indeed, in a treatment-seeking sample with PTSD, Jerud et al. [32] found no baseline differences in emotion regulation between those with and without history of child abuse. They further observed equivalence in improved emotion regulation between these groups following treatment, despite no prior emotion regulation training. Notwithstanding, it is acknowledged that omission of emotion regulation training may limit the potential success of the current iCBT program for some survivors of child trauma.

## Trial status

This article was first submitted on 19 June 2015. To date, 26 participants have met eligibility requirements. The first round of applications opened on 12 September 2014 and the first participant was enrolled on 13 September. Data collection aims to be complete in September 2016.

## Abbreviations

ANOVA: Analysis of variance
BDI-II: Beck Depression Inventory – Second Edition
CBT: Cognitive behaviour therapy
CEQ: Credibility and Expectancy/Satisfaction Questionnaire
CRUfAD: Clinical Research Unit for Anxiety and Depression
DES: Dissociative Experiences Scale
DSM-IV: Diagnostic and Statistical Manual of Mental Disorders, Fourth Edition
DSM-5: Diagnostic and Statistical Manual of Mental Disorders, Fifth Edition
ERQ: Emotion Regulation Questionnaire
GAD: Generalised anxiety disorder
GAD-7: Generalised Anxiety Disorder 7-Item Scale
HREC: Human Research Ethics Committee
iCBT: Internet-delivered CBT
ITT: Intent-to-treat
IU: Intolerance of uncertainty
IUS-12: Intolerance of Uncertainty Scale 12-item version
K10: Kessler Psychological Distress Scale 10-item version
LEC-IV: Life Events Checklist for DSM-IV
LEC-5: Life Events Checklist for DSM-5
MAR: Missing at random
MINI: Mini International Psychiatric Interview
OCD: Obsessive compulsive disorder
PCL-C: PTSD Checklist – Civilian version
PCL-5: PTSD Checklist for DSM-5
PHQ-9: Patient Health Questionnaire 9-item version
PTE: Potentially traumatic event
PTSD: Posttraumatic stress disorder
RCT: Randomised controlled trial
REML: Restricted maximum likelihood estimation
SAPAS: Standardised Assessment of Personality – Abbreviated Scale
SP: Social phobia
SPIRIT: Standard Protocol Items: Recommendations for Interventional Trials guidelines
SPSS: Statistical Package for the Social Sciences
SUDOR: Service Utilisation and Days Out of Role Questionnaire
